## Abstract

**Background:**

Total knee replacement (TKR) is a common and effective surgical procedure to relieve advanced knee arthritis that persists despite comprehensive medical treatment. Although TKR has excellent technical outcomes, significant variation in patient-reported functional improvement post-TKR exists. Evidence suggests that consistent post-TKR exercise and physical activity is associated with functional gain, and that this relationship is influenced by emotional health. The increasing use of TKR in the aging US population makes it critical to find strategies that maximize functional outcomes.

**Methods/Design:**

This randomized clinical trial (RCT) will test the efficacy of a theory-based telephone-delivered Patient Self-Management Support intervention that seeks to enhance adherence to independent exercise and activity among post- TKR patients. The intervention consists of 12 sessions, which begin prior to surgery and continue for approximately 9 weeks post-TKR. The intervention condition will be compared to a usual care control condition using a randomized design and a probabilistic sample of men and women. Assessments are conducted at baseline, eight weeks, and six- and twelve- months. The project is being conducted at a large healthcare system in Massachusetts. The study was designed to provide greater than 80% power for detecting a difference of 4 points in physical function (SF36/Physical Component Score) between conditions (standard deviation of 10) at six months with secondary outcomes collected at one year, assuming a loss to follow up rate of no more than 15%.

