### Recruitment, baseline assessment and randomization

The study coordinator recruits patients by reviewing a list of patients each week who are scheduled for upcoming TKR surgery, assessing patient's eligibility, calling patients to introduce the study and then mailing the consent form. The coordinator then follows up via telephone call. Patients complete and mail back a baseline assessment that includes the SF-36, the Pre-Surgery WOMAC, and a modified arthritis and exercise Self-Efficacy Scale. In addition, participants wear an ankle accelerometer (Step Activity Monitor) for four continuous days (at least one weekend day), and complete an exercise log.

Upon completing the baseline assessment, each patient is randomized into the Patient Self-Management Support intervention or to a usual care (control) condition. The study uses a stratified simple random sampling (S-SRS) of TKR patients to assure that participants represent subgroups of patients who may respond differently to the intervention. Patients are stratified by gender (two categories), BMI (three categories, < 30, 30-35, and > 35), and emotional health (SF36/Mental Composite Score; MCS) (three categories, < 45, 46-60, and > 60). This sampling scheme ensures that the sample includes wide variation in pre-operative BMI and MCS and gender balance. The categories are based on the distribution of pre-operative measures in a national sample. There are 2 × 3 × 3 = 18 strata in total. Within each stratum, 5 patients are randomized to intervention group and 5 to control group. The order of the two blocks is randomly permuted. Total target enrollment for the trial is 180 patients.

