#### Sample size considerations and statistical analyses

##### Sample size estimation

Sample sizes were calculated using the method developed by Frison and Pocock [37] with the SF-36 PCS as the primary outcome. Because patients are randomized within surgeon, we assume complete randomization of the study subjects to each treatment arm. We used the mean changes of repeated measures to estimate the required sample sizes based on Analysis of Covariance (ANCOVA) method. The mean change is defined as the difference between each subject's mean post-treatment PCS (the mean of 6 and 12 month PCS) and the baseline measurement.

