##### Effect Size

This trial was designed to determine whether the intervention will outperform the control by 4 or more points in the SF36 PCS. This effect size is approximately one-half of the PCS standard deviation and 40% of the mean pre-post PCS TKR change of 10.5 points reported in the PORT study. Based on our pilot data and the national registry of TKR patients, mean post-PCS scores are assumed to be 39.5 and 43.5 for the control and intervention arms, respectively; the standard deviation of post-TKR PCS is estimated as 10.9 for pre-and post-intervention periods and the autocorrelation coefficient between the post treatment measurements across time for PCS is 0.65, and between pre-and post treatment measures is 0.50 [4]. One pre-intervention and two post-intervention measurements were completed (6 and 12 months). Assuming 75 completers per condition after attrition or exclusion due to missing data, the trial is capable of detecting an intervention effect of a change of 4 or more points on the SF36 PCS with statistical power in excess of 0.83 at two-sided significance level of 0.05, or 0.90 at one-sided significance level of 0.05. Secondarily, a 10 point difference in change in WOMAC physical functional scores between the arms can be detected with > 85% power at 5% significance level.

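### The abstract's power claim (six months, SD 10) and the only calculation shown (mean of 6 and 12 months, SD 10.9) describe different designs; with SD 10.9, six-month power is about 74%

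*Protocol article*

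**What the plan says.** Abstract, Methods/Design: power above 80% is claimed for a 4-point PCS contrast, described as "between conditions (standard deviation of 10) at six months with secondary outcomes collected at one year, assuming a loss to follow up rate" (the cap given is 15%). Six months is thus the powered time point, the SD is 10, and one-year outcomes are secondary.

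Sample size estimation: the method is ANCOVA for repeated measures (Frison and Pocock). The powered quantity compares two things for each subject: "the mean of 6 and 12 month PCS) and the baseline measurement". The 12-month value is therefore part of what was powered.

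Effect Size: "the standard deviation of post-TKR PCS is estimated as 10.9 for pre-and post-intervention periods". The correlation is 0.65 between post-treatment measures and 0.50 between pre- and post-treatment measures. With 75 completers per arm, the stated power for 4 points is above 0.83 (two-sided 5%) or 0.90 (one-sided 5%). Of the 4 points, the same section says: "This effect size is approximately one-half of the PCS standard deviation".

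Analysis Plan: the primary outcome is the change in PCS at 6 or 12 months, in a model with treatment, time point and their interaction, adjusted for baseline function among other covariates.

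**The concern.** The abstract and the sample size text differ on two inputs that drive power: the SD (10 against 10.9) and the endpoint (one visit against the average of two). Averaging two visits correlated at 0.65 reduces the variance, so power calculated for the average does not carry over to one of the visits. The document shows no calculation for six months alone.

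At stake is how a six-month result would be read. The abstract presents six months as the powered time point, and the Analysis Plan leaves the choice between 6 and 12 months open. A reader would credit a null six-month result with more than 80% power, although the SD in the sample size section does not give that. The one-half SD description also makes the target effect look larger, relative to patient variability, than it is.

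**Working it through.** **Inputs.** Difference 4 points (39.5 against 43.5), SD 10.9, correlations 0.65 (post-post) and 0.50 (pre-post), 75 completers per arm, two-sided 5%: all from Effect Size. SD 10, six months and loss of at most 15%: Abstract. Enrolment of 180, 1:1: Recruitment section. A 15% loss leaves 180 × 0.85 / 2 = 76.5 per arm.

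**Formulas.** Residual SD = SD × √f, with f the ANCOVA variance factor. SE = residual SD × √(2/n). Power = Φ(4/SE − 1.960).

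**1. Reproduce the stated figure (mean of 6 and 12 months, SD 10.9, n = 75).**
- f = (1 + 0.65)/2 − 0.50² = 0.575
- Residual SD = 10.9 × √0.575 = 8.27
- SE = 8.27 × √(2/75) = 1.350, and 4/1.350 = 2.96
- Power = 84.2% two-sided (83.8% with the noncentral t) and 90.6% one-sided

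This agrees with the stated 0.83 and 0.90, so the method and inputs have been read as intended.

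**2. Six months alone, same inputs.** Only the pre-post correlation enters.
- f = 1 − 0.50² = 0.75
- Residual SD = 10.9 × √0.75 = 9.44
- SE = 9.44 × √(2/75) = 1.541, and 4/1.541 = 2.60
- Power = 73.7% (73.2% with the noncentral t); with 76.5 per arm, 74.6%
- Difference detectable with 80% power = (1.960 + 0.842) × 1.541 = 4.3 points
- Completers needed for 80% power at 4 points: 88 per arm
- With SD 10.9 and 75 per arm, 80% power would need a pre-post correlation of about 0.60, not 0.50

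**3. Six months alone with the abstract's SD of 10, baseline-adjusted.**
- Residual SD = 10 × √0.75 = 8.66
- Power = 80.7% with 75 per arm and 81.5% with 76.5 per arm

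| Endpoint (ANCOVA, r = 0.50) | SD 10 | SD 10.9 |
|---|---|---|
| Six months, 75 per arm | 80.7% | 73.7% |
| Mean of 6 and 12 months, 75 per arm | 89.8% | 84.2% |

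**4. Standardised effect.** 4/10.9 = 0.37 and 4/10 = 0.40. One-half would require an SD of 4/0.5 = 8.

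**The case against.** A reader might infer that the abstract's power is simply a wrong calculation. The documents do not support that. The abstract states its own SD, and with SD 10, the planned baseline adjustment and a correlation of 0.50, six-month power does exceed 80%, by about one point. The figure in Effect Size also reproduces. This part of the objection stands. It does not remove the conflict: the SD of 10 appears only in the abstract and without a source, while Effect Size attributes its planning values to pilot data and a national registry. Nor can 10 be passed over as a rounding of 10.9, because that difference alone moves six-month power across 80%.

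A reader might also calculate an unadjusted six-month comparison and find a much larger shortfall. That is not the planned test: the sample size method is ANCOVA, and the Analysis Plan adjusts for baseline function.

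A third tempting inference is that 75 completers of 90 (16.7% loss) contradicts the abstract's 15%. It need not. The 15% is loss to follow-up, whereas the 75 also allows for exclusion because of missing data. The two are compatible, and the difference moves power by less than one percentage point.

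It is also fair to say that the Analysis Plan describes a model over both time points with several covariates, so 74% is not the power of that whole model, and that no sample size depends on the one-half SD remark. Both are accepted. The remark is close to 4/8.27 = 0.48, the ratio to the residual SD of the two-visit mean, but the text names the PCS standard deviation.

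**Conclusion.** The point holds as an inconsistency in SD and powered endpoint between the abstract and the sample size text. The abstract's claim of more than 80% power at six months is not delivered by the SD that the sample size section uses: power there is about 74%, some 10 percentage points below the 84% for the two-visit mean. This rests on a single-visit ANCOVA adjusted for baseline only, SD 10.9, pre-post correlation 0.50, 75 completers per arm and a two-sided 5% test. If SD 10 is the better planning value, six-month power is about 81%, and it is then the sample size section that needs the matching SD.

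The standardised effect is wrong as written: 0.37 SD, not about one-half. This is a descriptive error that does not enter the power calculation. Neither part calls the sample size of 180 into question for the two-visit mean.

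**What to change.** Reconcile the Abstract, Sample size estimation, Effect Size and Analysis Plan on one primary time point and one SD, then state the power that belongs to them. With SD 10.9 and 75 completers per arm, at two-sided 5%:

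- if the primary is the baseline-adjusted mean of 6 and 12 months, about 84%;
- if the primary is six months alone, about 74%, with a difference of about 4.3 points detectable at 80% power.

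The sponsor should make the choice of time point explicitly; harmonising the power figures should not make it by default. If SD 10 is kept, give its source and use it throughout.

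In Effect Size, replace the one-half SD description with about 0.37 SD.

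The cost is a less favourable stated power if six months is the primary time point. Restating the figures needs no extra patients.

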**Discussion:**

As TKR use expands, it is important to develop methods to identify patients at risk for sub-optimal functional outcome and to effectively intervene with the goal of optimizing functional outcomes. If shown efficacious, this peri-TKR intervention has the potential to change the paradigm for successful post-TKR care. We hypothesize that Patient Self-Management Support to enhance adherence to independent activity and exercise will enhance uniform, optimal improvement in post-TKR function and patient autonomy, the ultimate goals of TKR.

**Trial Registration:**

ClinicalTrials.gov: NCT00566826

## Background

The number of primary total knee replacement (TKR) procedures has grown by 73% in the past 10 years [1] and is projected to expand by more than 600% to 3.48 million procedures by 2030 [2]. Several facts are responsible for this increase in use, including (1) the prevalence of knee arthritis parallels the growing numbers of older adults, (2) increasing numbers of working aged adults are choosing TKR [1], and (3) TKR is a cost-effective intervention that reduces and eliminates pain. Despite these encouraging facts, significant variation remains in patient-reported functional improvement after TKR. An estimated 15-38% of patients report minimal functional improvement at 12 months, while another 10% report functional gains up to 3 times the national average [3,4]. Furthermore, our data suggests that the distribution of physical function at 12 months after TKR is bimodal [5]. The mechanism that underlies this varied functional improvement is not understood. While TKR researchers have identified some consistent predictors of poor gains in post-TKR function, no one patient attribute or surgical factor offers a satisfactory explanation for this outcome variation [6]. Importantly, poor emotional health as measured by the Mental Composite Score (MCS) of the SF36 is consistently associated with poor functional gain following TKR [3,4]. The NIH TKR Consensus Panel called for further research to address the role of patient attributes and rehabilitation regimens in functional outcome after TKR.

Exercise and activity improve global and knee-specific function in knee arthritis patients [7] and patient's confidence in their ability to manage their arthritis pain and function has been consistently associated with improved function, exercise, pain control, and self-care [8]. We have examined these associations in our pilot research and our data support a direct relationship between quantity of post-TKR exercise and activity and functional gain after TKR. This relationship was mediated by the patient's emotional health (SF36, MCS) and MCS was directly correlated with self-efficacy for arthritis self-care [9].

Based on the existing evidence, we hypothesize that a Patient Self-Management Support intervention that targets self-efficacy for physical activity and independent activity and exercise during the peri-operative TKR period will improve actual adherence to independent exercise and activity and, thus, maximize 6 and 12 month functional outcomes among post- TKR patients. This paper describes an ongoing study that is testing this hypothesis.

## Methods/Design

### Study Design

This prospective randomized clinical trial (RCT), funded by the National Institute for Arthritis and Musculoskeletal and Skin Diseases; NIAMS), is testing the efficacy of a theory-based telephone-delivered patient self-management support intervention to optimize post-TKR patient functional outcomes. The study participants are randomized to the Patient Self-Management Support intervention or to a usual care (control) condition, defined as care as prescribed by the patient's orthopedic surgeon or health care provider. The study seeks to assess the effect of the intervention on post TKR functional improvement, and understand the mechanisms of intervention effect by evaluating the roles of home exercise, physical activity, exercise self-efficacy, and participant attributes on functional improvement after TKR. It is hypothesized that, as compared to the control condition, patients receiving the Patient Self-Management Support intervention will have significantly greater increase in 6 and 12 month global (SF36/PCS) and knee-specific (WOMAC-Western Ontario and McMaster Universities Osteoarthritis Index) function. We also hypothesize that the intervention will enhance self-efficacy for exercise and that, in turn, increased self-efficacy will be associated with higher levels of home exercise and physical activity at 8 weeks and 6 and 12 month post-TKR. The study has approval from the Institutional Review Board of the Office of Human Subjects at the University of Massachusetts Medical School.

### Setting and population

The study is being implemented in collaboration with the Arthritis and Joint Replacement Center at UMass Memorial Medical Center (UMMHC), Worcester, MA, the sole dedicated arthroplasty center for the UMMHC 7-hospital system. Men and women 21 years of age or older and scheduled for primary, single-side TKR surgery undergoing surgery at the Arthritis and Joint Replacement Center are eligible for participation. Exclusions include: inflammatory arthritis, TKR due to fracture, malignancy, infection, or failure of a previous arthroplasty; inability to provide informed consent due to dementia or cognitive impairment; co-existing conditions that would negate functional improvement with surgery and exercise (i.e., severe Parkinson disease, or hemi paresis); emergently scheduled surgery; simultaneous bi-lateral TKR; terminal illness with life expectancy of less than one year; expected to be community dwelling after surgery; unavailable to complete the study procedures (i.e., will be out-of-region during rehabilitation period); and planning another TKR or total hip replacement surgery within 6 months.

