#### Study assessments

Data are collected at baseline prior to surgery and at 8 weeks, 6 months, and 12 months post-TKR. Sources of data include: (1) patients, (2) surgical records, (3) physical therapy records, and (4) data recorded by the intervention coach in the intervention database. The following section describes individual measures used to assess outcomes of interest.

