##### Exercise and Activity

A *Step Activity Monitor *(accelerometer) assesses mean steps per day and activity intensity (steps per minute). The monitor provides a summary of total number of steps/cycle per 24 hour period and percent time/day that the individual is active at high/moderate/low activity, % of day inactive, and maximum sustained intensity for 5 and 30 minutes [31]. In addition, participants complete an *exercise (paper) log *to record the number of daily exercise sessions, repetitions and sets for each of the core home-based physical therapy exercises. The log is completed at 8 weeks and 6 months.

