##### Analysis Plan

We will test the self-care support program's effect, both overall and in the latent low and high function response groups, as predicted by baseline characteristics on post-TKR 6 and 12 month functional outcome. We will apply mixture models with two latent classes (or GLLAMM), where the post-operative change in global function (PCS/SF36) at 6 or12 months is the primary outcome. The main predictors of the model include intervention indicator (0 = control versus 1 = intervention), data collection time points, and the interaction term between intervention indicator and time points. The treatment effects will be evaluated by testing the significance of the coefficient of intervention indicator and an interaction term of time and the intervention indicator. In the analysis, we will adjust for other patient characteristics that may moderate the intervention effect or reduce unexplained variability including gender, age, baseline function score, BMI, depression, anxiety, or social support. Potential moderating effects of each variable on the intervention will be examined by including interaction terms with the intervention indicator. The intervention effects on changes in knee pain, function using WOMAC sub-scores, number of daily repetitions and mean steps/hour on step activity monitor, and self-efficacy scores) will be analyzed using similar approaches. If the proposed intervention is effective, the post-TKR increases in home exercise and activity levels, and self-efficacy score in the intervention condition should be significantly greater than in the control condition. Next, we will examine whether the improvement in Stanford Arthritis Self-Efficacy scores predicts increases in home exercise and activity levels. Using a similar approach, we will test whether higher levels of home exercise (number of daily repetitions) and physical activity (mean steps/day on accelerometer) at 8 weeks post-TKR are associated with greater improvement in 6 and 12 month post-TKR global physical function and knee function.

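### One exclusion criterion appears to have lost its negation: as written, patients expected to live in the community after surgery are excluded

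*Protocol article*

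**What the plan says.** The Setting and population section states inclusion first: adults of 21 or older who are scheduled for a primary, single-side TKR at the center. A single list separated by semicolons follows, opened by "Exclusions include: inflammatory arthritis, TKR due to fracture, malignancy, infection, or failure of a previous arthroplasty". A later item in that list reads "expected to be community dwelling after surgery". It has no negation of its own, and no new lead-in separates it from the exclusions before and after it.

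Other sections describe the setting that the trial needs:

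- Study Design names home exercise and physical activity among the mechanisms to be evaluated.
- Intervention Structure and Content places seven of the 12 sessions after discharge, in weeks two to nine, and includes coaching on activity at home and on local activity groups.
- Exercise and Activity, under Mediators, describes a step monitor and a paper log of the "core home-based physical therapy exercises".

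The exclusion list closes with patients who are "planning another TKR or total hip replacement surgery within 6 months".

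**The concern.** Every other item in the list is a reason to keep a patient out. Read the same way, this item keeps out people who will live in the community after surgery, who are the people able to do and record independent exercise at home. The rule therefore points in the opposite direction to the intervention and its measurements.

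This is an operative rule and not background text. The coordinator assesses eligibility each week from the surgical schedule, and readers will use the same list to judge whom the result applies to or to repeat the trial. If the published criterion is the reverse of the intended one, the target population is misdescribed even if the trial itself was run correctly.

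**Working it through.** No arithmetic applies. The check is whether the item can be read in a way that agrees with the rest of the article.

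1. **Can it be an inclusion criterion?** No. Inclusion is complete in the sentence before. The item stands in the middle of the exclusion list, between a life expectancy below one year and being unavailable for study procedures, both of which are reasons to exclude.

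2. **Does another section correct it?** No. Community residence as a criterion appears only here. The abstract and the Study Design section do not restate eligibility on this point.

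3. **Does the literal rule agree with the intervention?** No. The intervention aims at adherence to independent exercise and activity, and seven of 12 sessions (7/12, or 58%) take place after discharge. Telephone sessions could in principle reach a patient in an institution, so their timing alone does not settle the matter. The coaching content on activity at home and in local groups does presuppose community living.

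4. **Does the literal rule agree with the measurements?** No. A log of home-based exercises would have little to record in a sample chosen for not living in the community. The Analysis Plan uses home exercise and step counts at 8 weeks as predictors of functional gain at 6 and 12 months.

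5. **Does the negated rule agree?** Yes. With *not* inserted, the item excludes patients who are not expected to live in the community. That fits its neighbor, which removes people who will be away during rehabilitation, and it agrees with everything in steps 3 and 4.

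6. **Does a figure in the plan depend on it?** No. The sample size rests on PCS means, a standard deviation, correlations and 75 completers per arm. None of these changes with the wording of this item.

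**The case against.** The best defense is that the meaning is plain. Any informed reader of a home-exercise trial would supply the missing word, and a journal article is not the document from which patients are screened. Most of this stands. It is a drafting slip and not a design decision, and the screening documents, which are not shown, may well carry the correct wording. It does not make the published criterion right, and no other sentence in the article puts it right.

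Three stronger readings are tempting, and the article does not support them.

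- *The trial enrolled the wrong patients.* That would follow only if screening had used the reversed wording, and nothing in the article shows this.
- *The main outcomes depend on home records.* The log and step counts are listed as mediators. The main outcomes are the SF-36 and the WOMAC. The Analysis Plan does analyze repetitions and steps, but not as the primary outcome.
- *The 6-month limit on a planned second replacement is also an error that distorts the primary outcome.* The limit fits the abstract, which powers the trial at six months and places secondary outcomes at one year. The article gives no rate of second surgery. Randomization should spread such operations over both arms, so the expected effect is some dilution and noise. Whether to exclude for 12 months is a trade-off against recruitment and generalizability.

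**Conclusion.** The point holds as an internal contradiction in the eligibility criteria. As written, the list excludes the population that the intervention and its home-based measurements require. The most probable cause is a lost *not*; this is an inference from the rest of the article, though no other reading fits it.

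The effect on the trial itself is unknown. It is nil if the screening documents carry the intended criterion. It would be fundamental if they carry the printed one, but the article gives no ground for assuming so.

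The second-surgery limit is not part of this finding. At most, it should be reconciled with the primary time point, which the article states inconsistently. The abstract gives six months, Sample size estimation uses "the mean of 6 and 12 month PCS", and the Analysis Plan says that "the post-operative change in global function (PCS/SF36) at 6 or12 months is the primary outcome".

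**What to change.** Insert *not* before "expected to be community dwelling after surgery" in Setting and population, so that the item agrees with Study Design, Intervention Structure and Content, and Exercise and Activity. Then confirm from the screening form and log that the intended criterion was applied to the patients assessed so far, and record the result. The article describes the study as ongoing, so this check should be feasible.

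The correction is one word. The check takes a short review of existing records and affects neither recruitment, the sample size nor the analysis. When the primary time point is settled, state in the same revision when the 6-month limit on a planned second replacement starts and how it relates to that time point.
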